#### Conventional treatment in both groups

2.5.2

According to the clinical guidelines for the treatment of TBE, all the participants will undergo conventional treatment, which involves general management in the Department of Neurosurgery to stabilize vital signs, the medicine or the surgery to reduce ICP, neuroprotective medicines, treatment of infections, and other intravenously administered fluid or drug therapy required according to the condition of the patient. However, it is not allowed to give patients treatments that reduce ICP or improve brain function outside of this study. During the clinical trial period, all treatments, including acupuncture needles and medications, will be inspected by investigators who will record any changes and the reasons for them.

#### Discontinuing interventions

2.5.3

The trial will be ceased if one of the following conditions appears: development of serious complications or any other severe condition that leaves the patient in a critical condition; serious adverse reactions and an inability to continue the trial; withdrawal of consent; or a decision by the principal investigator that it is not possible for the patient to participate in the study as planned.

### Outcome measures

2.6

#### Primary outcome

2.6.1

The primary outcome is the functional status of patients with TBE according to a dichotomized GOS (poor recovery = GOS 1∼3; good recovery = GOS 4∼5) at 6 and 12 months after the injury.

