### Follow-up

2.7

After 4 weeks of complement acupuncture treatment, the trial will enter a follow-up period till 12 months after injury, when all participants receive the equal therapy as possible follow-up on a monthly basis via telephonic and message communications or outpatient review, treatment compliance and changes of clinical manifestations will be faithfully recorded. The data of 6-month and 12-month will be used for the final statistical analysis of the trial.

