### Sample size calculation

2.9

Because the data available for patients with TBE who receive early acupuncture treatment are limited and inconclusive, we will perform a single-blind RCT in which the control group will receive conventional treatment and the study group will receive additional acupuncture as an adjuvant therapy. The primary outcome will be dichotomized GOS (poor recovery = GOS 1∼3; good recovery = GOS 4∼5) at 6 and 12 months of follow-up after the injury. According to our previous pilot study, the change of GOS (good recovery rate) in the study group was shown to be 80% (n = 12), and that in control group was 50% (n = 12). Sample size was calculated using the Power Analysis and Sample Size (PASS) software package (version 15, NCSS, Kaysville, UT), with a 2-sided significance level (α = 0.05), a power of 80%, and chi-squared tests to assess the difference in rates between the 2 groups. Thus, a total sample size of 80 participants (40 per group) will be recruited, allowing for 10% loss during follow-up.

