### Statistical analysis

2.10

After a patient has been randomly assigned, the outcome measures will be collected even if the trial treatment is interrupted or not given. The data used will include the method of the last observation carried forward or the method of the worst observation carried forward.^[26]^ That is, this study will analyze the data with the full analysis set.

The statistical analyses will be performed by a blinded researcher. According to the intention-to-treat principle, all the data will be analyzed using the SPSS statistical software package (version 20.0, IBM SPSS Statistics, IBM Corp, Somers, NY). Baseline characteristics will be described and compared. Continuous variables subject to normal distribution will be presented as the mean ± standard deviation; continuous variables not subject to normal distribution will be expressed as the median and interquartile range; and categorical variables will be described as the frequency and percentage.

GOS, wake-promoting rates, and adverse events rates will be compared using the chi-squared or Fisher's exact tests. GCS and MBI scores will be compared between the 2 groups by *t* test with a 95% confidence interval. The results of the volume of TBE and the serum levels of CRP and IL-6 between the 2 groups will be compared using either a generalized linear mixed model or the *t* test, and repeated contrast tests will be conducted to account for time differences in each group. If the data are not normally distributed, nonparametric methods will be used. For all analyses, the results with a *P* value less than .05 will be considered statistically significant. The clinical efficacy should be determined in the evaluation of clinical significance.

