## Discussion

3

TBE, the most frequent cause of death after TBI, is an independent risk factor for neurological unfavorable prognosis.^[3,4]^ TBE occurs commonly as pericontusional edema of brain contusions, which leads to a life-threatening increase in ICP. In evidence-based medicine, no treatment measures other than craniotomy and mannitol have been recommended for TBE.^[6]^ Thus, more effective and safe strategies to improve the outcome of patients with TBE are urgently needed. As a complementary and alternative therapy, acupuncture has been widely used to treat neurological diseases, and the effect of acupuncture on patients with TBI has been certified by some studies.^[28,29]^

Here, we describe the protocol of a single-center, single-blinded, RCT to determine if the addition of complementary acupuncture for TBE on acute phase is more effective than conventional treatment alone. We also aim to determine whether acupuncture has an anti-inflammatory effect and is associated with a reduction in the volume of brain edema. This RCT selects appropriate participants and controls confounding factors to optimize clinical evaluation of efficacy.

In this RCT of conventional treatments combined with acupuncture for TBE, we chose drug therapy (i.e., mannitol) as the conventional treatment to reduce ICP, because mannitol is commonly used clinically and is recommended by evidence-based medicine. Also, the optimal timing of acupuncture therapy for TBE is unclear. We relied on expert consensus and clinical guidelines that considered the safe and feasible approach when acupuncture therapy started within 72 hours after injury.^[30,31]^

In this study, the acupuncture points were selected based on traditional Chinese medicine theory, our previous pilot study, and summaries of the medical experts’ experiences. For example, the acupuncture points of GV26, PC6, and SP6 were selected on the basis of Shi's Xingnaokaiqiao theory, which has achieved significant effects in the treatment of acute and critical cerebrovascular diseases.^[32]^ In addition, Chen has used the acupuncture points of GV20, GV26, GB20, LI4, and LR3 to treat neurological diseases and achieved satisfactory clinical curative effects in improving brain function.^[33]^

Among the scores measuring functional recovery and quality of life after TBI, GOS is the most reliable, most validated, and most used score in RCTs.^[34]^ We defined the GOS at 6 and 12 months as the primary outcome.

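### GOS at 6 and at 12 months are both primary, each open to a test at P < .05 with no rule joining them; the 80 patients cover one comparison only

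*Protocol article*

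**What the plan says.** Section 2.6.1 (Primary outcome) defines the outcome as the GOS split into poor (1 to 3) and good (4 to 5) recovery, assessed "at 6 and 12 months after the injury". The Abstract and section 2.9 repeat both time points, and the Discussion confirms the choice: "We defined the GOS at 6 and 12 months as the primary outcome". Section 2.7 (Follow-up) sends both to the final analysis: "The data of 6-month and 12-month will be used for the final statistical analysis of the trial". Nowhere is one placed before the other.

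Section 2.10 (Statistical analysis) gives the test: "GOS, wake-promoting rates, and adverse events rates will be compared using the chi-squared or Fisher's exact tests". The mixed model in the same section is offered only for edema volume, CRP and IL-6. The threshold is general: "For all analyses, the results with a *P* value less than .05 will be considered statistically significant".

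Section 2.9 (Sample size calculation) uses one pair of pilot rates (80% in the study group, 50% in the control group, n = 12 each), one two-sided alpha of 0.05, one power of 80%, and "chi-squared tests to assess the difference in rates between the 2 groups". It arrives at 80 participants, 40 per group, including 10% loss. It does not say at which time point the pilot rates were observed.

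**The concern.** A chi-squared or Fisher's exact test compares two groups on one binary result. Two primary time points therefore mean two primary tests, and the only stated criterion is P < .05 for each. The reader cannot tell what counts as a positive trial:

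- **Either time point suffices.** The trial has two chances of a false positive, and the 5% in section 2.9 no longer describes the whole primary analysis.
- **Both are required.** The false-positive rate stays at or below 5%, but the chance of success falls below the 80% in section 2.9.

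The harder case is a split result, for instance significant at 6 months and not at 12. With no rule fixed beforehand, the choice of which result is the trial's answer could follow the data.

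**Working it through.** **Inputs from the protocol article.** Good-recovery rates 0.80 and 0.50, two-sided alpha 0.05, power 80%, 10% loss, 40 per group (section 2.9); 1:1 allocation (section 2.4); P < .05 throughout (section 2.10).

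**Assumptions, not in the document.** The correlation ρ between the 6- and 12-month test statistics, shown from 0.5 to 0.9; and, for joint power, the same effect at both time points.

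**1. Reproduce the plan's figure.** Unpooled-variance formula for one comparison:

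n = (1.960 + 0.842)² × (0.80×0.20 + 0.50×0.50) / 0.30² = (1.960 + 0.842)² × 0.41 / 0.09 = 35.76, so 36 per group.

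36 / 0.90 = 40 per group, 80 in total. This matches exactly, so 80 is the size for one test at the full alpha. There is no margin for a second: the pooled-variance formula for the same single comparison gives 39 per group, and 39 / 0.90 = 43.3, so 44 per group, 88 in total.

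**2. False-positive rate if either time point counts.** Rate = 1 − P(|Z₁| < 1.96, |Z₂| < 1.96), with (Z₁, Z₂) bivariate standard normal with correlation ρ. For independent tests this is 1 − 0.95² = 9.75%.

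**3. Joint power if both must be significant.** With each test at 80% power, joint power = P(Z₁ < 0.842, Z₂ < 0.842). For independent tests this is 0.80² = 64%.

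| ρ (assumed) | Type I error, either counts | Power, both required |
|---|---|---|
| 0.5 | 9.07% | 68.7% |
| 0.6 | 8.75% | 69.9% |
| 0.7 | 8.35% | 71.3% |
| 0.8 | 7.81% | 72.9% |
| 0.9 | 7.04% | 75.0% |

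The type I error equals 5% only at ρ = 1.

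**4. What each remedy needs, using the formula that reproduces 80.**

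- One primary time point, or a fixed order with the first test at .05: 36 evaluable, 40 per group, 80 in total, unchanged for the first test.
- Alpha split equally (0.025 each), 80% power per test: (2.241 + 0.842)² × 0.41 / 0.09 = 43.3, so 44 per group; 44 / 0.90 = 48.9, so 49 per group, 98 in total. If the trial stays at 36 evaluable per group, power per test at 0.025 is 71.6%.
- Both required with 80% joint power: 45 to 41 evaluable per group for ρ from 0.5 to 0.9, which is 50 to 46 with loss, 100 to 92 in total.

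**The case against.** **Inflation is conditional.** The article never says that success at either time point is enough. Under a both-required rule the type I error is not inflated. This is correct, but that rule breaks the power claim instead, so one of the two figures in section 2.9 fails either way. The blanket threshold also reads more naturally as each test standing alone.

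**The figures rest on a normal approximation and an assumed correlation.** Simulating the either-counts rule with 36 or 40 per arm, a null good-recovery rate of 50% or 65% and within-patient correlation 0.5 to 0.9 gives about 6.4% to 10.3% with the uncorrected chi-squared test, but only about 3.5% to 6.1% with Fisher's exact test. Section 2.10 allows both. Fisher's test is conservative at this size and could absorb much of the excess. Expected counts point to chi-squared, however: at 36 per arm and 65% good recovery overall, the smallest expected cell is 36 × 0.35 = 12.6. The same patients are measured twice and section 2.10 allows the last observation to be carried forward, so the correlation is probably towards the high end, where the excess is smallest.

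**The rule may sit in an unseen analysis plan.** A fixed order at .05 would be compatible with the stated threshold, so an analysis plan could supply one. Reduced alpha levels would contradict section 2.10 as written. Which time point is primary, and what counts as success, belongs to the definition of the outcome, which the article gives in full and leaves unordered.

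**The trial is called a feasibility study.** The Discussion does so, but it also says the results may change recommendations, and section 2.9 presents a formally powered hypothesis test.

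Nothing here supplies the missing rule. What stands is that the size of the inflation is uncertain and depends on the rule and the test used.

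**Conclusion.** The concern holds. Two unranked primary time points, a general P < .05 and a sample size built for one unassigned comparison do not fit together. If either time point counts, the overall two-sided error is about 7% to 9%; if both are needed, joint power is about 69% to 75%. Both ranges rest on an assumed correlation of 0.5 to 0.9, and the power range also on 80% power at each time point. The arithmetic behind 80 is right for one test; the fault is that the plan does not say which test that is and makes no allowance for the other. This should be settled before outcomes are known, because it determines the trial's main result.

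**What to change.** In section 2.6.1, name one time point as the single primary outcome and make the other key secondary. If both are to keep confirmatory status, state a fixed order in section 2.10: test the second at .05 only if the first is significant. Holm's procedure is a further option, but the smaller of the two P values must then fall below .025, so its power would have to be recalculated. In section 2.9, state which time point the 80%, the 50% and the 80% power refer to. Align the Abstract and the Discussion with the choice.

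The cost is about one sentence in each of sections 2.6.1, 2.9 and 2.10, ethics committee approval of the revision as section 2.11 requires, and an update of the trial registration if it carries the same definition. A single primary time point or a fixed order needs no more than the planned 80 patients for the first test. The price is that one time point no longer stands alone as confirmatory evidence.

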#### Secondary outcomes

2.6.2

The secondary outcomes are wake-promoting rates, changes in the GCS (Baseline GCS is used as the basis for grouping), the volume of TBE calculated by CT scan (i.e., the volume of brain contusions and pericontusional edema), and the serum levels of CRP and IL-6 measured at four different time points (baseline and days 7, 14, and 28 after treatment). Another secondary outcome, the Modified Barthel Index (MBI), will be measured at the beginning of treatment, at the end of 28-day treatment, at the 6-month and 12-month follow-up after injury.

Calculating the volume of TBE, including the volume of brain contusions and pericontusional edema, by CT scan with the help of 3D Slicer software (version 4.8.1) might reduce the subjective impact of quantifying brain edema. 3D Slicer is a free, open source, and multi-platform software package widely used for medical, biomedical, and related imaging research; it has been jointly developed by multiple institutions and has been supported by the National Institutes of Health in the United States.

The Human IL-6 ELISA kit (Wuhan Fine Biotech Co., Ltd., China) or the Human C-Reactive Protein ELISA kit (Head Office in China Beckman Coulter Commercial Enterprise (China) Co., Ltd. Shanghai, China) will be used to determine the concentrations of IL-6 or CRP in the samples, and the data will be analyzed. Collected samples will be centrifuged for 15 minutes at 1000 × *g* and stored in a freezer at −80 C until they are ready for processing and analysis. Samples will be discarded after the analysis. The timepoints for assessment are listed in Table 2.

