### Randomization and blinding

2.4

To ensure a balanced sample size across groups over time, the study is using stratified block randomization in a 1:1 ratio that divides patients into 2 groups according to the GCS (scores of 6∼8 or 9∼12). The study will also apply block randomization method with a block size of 2 (post-craniotomy or no craniotomy).

Random numbers will be made by a computerized number generator list provided by a statistician not involved in the determination of eligibility or in the assessment of outcomes. The allocation of participants will be sealed in sequentially numbered, opaque envelopes.

After verification that a patient meets all the inclusion criteria and none of the exclusion criteria, and after the informed consent is signed by legal representative, the doctor responsible for the patient will assign a correlative number to the patient who will be allocated to either the study group or the control group.

The blinding of this study is limited because it is easily discernible that some patients are receiving acupuncture therapy, and the acupuncturist cannot be blinded. However, the outcome assessors and statistician will be blinded and unaware of patient allocation. During the whole research process, unblinding will be carried out after the statistical analysis is completed.

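### CT lesion volume is compared as measured while surgery to lower intracranial pressure is allowed in both arms; if later surgery removes lesion tissue, a worsening patient can count as an oedema reduction

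*Protocol article*

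**What the plan says.** - **Outcome.** Section 2.6.2 of the protocol article lists "the volume of TBE calculated by CT scan (i.e., the volume of brain contusions and pericontusional edema" as a secondary outcome. It is one of a list of measures "measured at four different time points (baseline and days 7, 14, and 28 after treatment".
- **Concomitant surgery.** Section 2.5.2 states that "all the participants will undergo conventional treatment", and this includes "the medicine or the surgery to reduce ICP".
- **Craniotomy in the design.** Section 2.4 mentions it as "block size of 2 (post-craniotomy or no craniotomy", which is a status known at randomisation. Elsewhere it appears only as a starting point for the 72-hour window and in an exclusion for craniotomy unrelated to brain injury.
- **Analysis.** Section 2.10 states: "The results of the volume of TBE and the serum levels of CRP and IL-6 between the 2 groups will be compared", by a generalized linear mixed model or a t test, with nonparametric methods if the data are not normal. Outcomes are still collected when study treatment stops, and the full analysis set is used with last or worst observation carried forward.
- **Interpretation.** The Introduction and Discussion treat a smaller oedema volume as an effect of interest.

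**The concern.** The outcome does not separate tissue that resolved from tissue that was taken out. A patient whose lesion grows, who is then operated on and whose next scan shows a small residual lesion, enters the comparison with a low volume. That patient would be read as a success although the operation was prompted by deterioration.

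Nothing in the article intercepts this:

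- The craniotomy factor in 2.4 covers only surgery before randomisation.
- The discontinuation rules in 2.5.3 do not stop outcome collection.
- Carry-forward replaces missing values, and a postoperative scan is not missing.

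What is at stake is the conclusion on oedema volume. If acupuncture reduces the need for surgery, more control patients lose volume at operation and the comparison is biased against acupuncture. If acupuncture increases that need, the bias runs in its favour.

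**Working it through.** **The plan's own figure.** The article gives no number for CT volume. Its sample size rests on good recovery (GOS 4 to 5) of 80% vs 50%:

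n = (1.960 + 0.842)² × (0.80×0.20 + 0.50×0.50) / 0.30² = 35.8, so 36 per arm; 36 / 0.90 = 40 per arm, 80 in total.

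This reproduces the stated 80. The CT outcome plays no part in it.

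**Inputs for the illustration.** From the article: 40 per arm recruited, 36 per arm after 10% loss, two-sided 0.05. Assumed, because the article gives none of them: change in volume with mean -10 mL and SD 15 mL in unoperated patients, a net surgical effect x of 10 or 25 mL, and the operated proportions q. The article specifies no change score for volume; change from baseline is used here for convenience.

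The 10 mL value corresponds to a patient who goes from 40 to 70 mL, is operated on and shows 20 mL. The change is -20 mL, which is 10 mL beyond the assumed -10 mL.

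**Formulas.**

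- Bias = x × (q in the arm with more surgery − q in the arm with less)
- Variance per arm = 15² + x² × q(1 − q)
- SE = √[(V₁ + V₂)/40]
- Chance that the arm with fewer operations is significantly worse, when there is no other difference ≈ Φ(bias/SE − 1.96); nominal 2.5%

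| Operated | x (mL) | Bias (mL) | V₁, V₂ | SE | Wrong-direction significance |
|---|---|---|---|---|---|
| 5% vs 15% | 10 | 1.0 | 229.8, 237.8 | 3.42 | 5% |
| 5% vs 15% | 25 | 2.5 | 254.7, 304.7 | 3.74 | 10% |
| 10% vs 30% | 10 | 2.0 | 234.0, 246.0 | 3.46 | 8% |
| 10% vs 30% | 25 | 5.0 | 281.3, 356.3 | 3.99 | 24% |
| equal | any | 0 | – | – | 2.5% |

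A simulation with t tests (40,000 trials per row) agrees to within about half a percentage point.

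**Power.** The same simulation with a true 10 mL benefit and 36 per arm gives:

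- no surgery: 80%
- 15% operated in both arms, x = 25 mL: about 67%, with no bias at all
- 10% (acupuncture) vs 20% (control), x = 10 mL: about 69%
- 10% vs 20%, x = 25 mL: 44%

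**Dependence on what surgery removes.** Assume a 30 mL baseline, -10 mL if unoperated, +10 mL for a worsening patient left unoperated, and 20% of the acupuncture arm vs 10% of control operated.

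- Surgery leaves 5 mL (change -25 mL): acupuncture 0.8×(-10) + 0.2×(-25) = -13.0; control 0.9×(-10) + 0.1×(-25) = -11.5; difference -1.5 mL, apparently favouring acupuncture.
- The same patients scored as worsened: -6.0 vs -8.0, difference +2.0 mL.
- Surgery leaves 30 to 40 mL: difference +1.0 to +2.0 mL, so the sign does not flip.

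**The case against.** **The premise is not stated.** The article speaks of surgery to lower pressure, not of removing the lesion. The Introduction itself notes that oedema can advance after craniotomy. Decompression that leaves the lesion would not shrink the measured volume. This stands, and it is why the point is conditional.

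**Late surgery may be uncommon.** The Discussion names mannitol as the chosen pressure-lowering treatment, patients with unstable vital signs within 72 hours are excluded, and some patients enter already operated on. This also stands. But 2.5.2 still permits surgery, and the Introduction names craniotomy as one of the few established treatments for this condition.

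**A statistical analysis plan could add a rule, and analysing volumes whatever standard care follows is a recognised treatment-policy estimand.** Both are fair. The as-measured comparison can therefore stay as the main analysis. The article has nevertheless fixed the measure, the analysis set and the family of tests, and the as-measured result alone does not show whether a lower volume reflects resolution or removal.

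**Stronger readings that a reader might infer.**

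- *An operated patient will show the largest reduction, or is scored as twice as good as one who recovers.* No change score is specified for volume, so no such ratio follows from the plan. In an assumed simulation of 80 patients with 4 operated, an operated patient had the largest reduction in 21% of trials when 10 to 30% of the lesion remained, 7% when 30 to 60% remained, and 0% when 90 to 140% remained.
- *Bias takes power from 80% to 44%.* That figure needs a 25 mL net effect, and much of the fall is variance: equal 15% rates already give about 67%.
- *Operated patients should be ranked worst in the main analysis.* Only outcome assessors and the statistician are blinded, so an unblinded decision to operate would then drive a blinded CT measure.

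**Conclusion.** The concern holds in a conditional form. As written, a scan taken after lesion-removing surgery is analysed as measured, and a patient who deteriorated can contribute an apparent oedema reduction. The comparison is biased towards the arm with more such operations, and even equal rates cost some power.

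On the assumptions above, with a net surgical effect of 10 to 25 mL, the bias is 1.0 to 2.5 mL at 5% vs 15% operated and 2 to 5 mL at 10% vs 30%. Wrong-direction significance is about 5% to 10% and 8% to 24% respectively, against a nominal 2.5%. The bias is nil if rates and types of surgery are equal. The documents support neither a particular size nor a direction. This concerns one secondary outcome, though one that the article names among its aims.

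**What to change.** In 2.6.2 and 2.10:

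1. Take the baseline volume from the last CT before randomisation. For patients entered after craniotomy this is a postoperative scan.
2. Keep the as-measured comparison, and report by arm the number, timing and type of cranial operations after the baseline CT.
3. Pre-specify, before unblinding, a sensitivity analysis in which volumes after a lesion-removing operation are not used as measured. One option is a rank comparison that places these patients below unoperated survivors, with deaths lowest. Claim an oedema reduction only if the two analyses agree in direction.

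The cost is one extra analysis and a slightly more cautious claim on a secondary outcome. Section 2.5.2 already has investigators record treatment changes and the reasons for them, so no new scan, visit or patient is needed.
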